**Fig. 1 Fig1:**
[figure not shown]
Study design and *flow chart*

### Data collection procedures

#### Pre- and post-training assessments to CHWs

Before starting CHW training, a self-administered questionnaire will be given to all CHWs from the intervention villages to assess their prior knowledge about CVD risk factors. The questionnaire will be adapted from the WHO training manual on NCDs and healthy lifestyle promotion. The tool will assess CHWs’ knowledge on: (1) causes and risk factors for CVDs; (2) warning signs for CVD events; (3) course of action to be taken in case of CVD events; (4) unhealthy dietary habits; and (5) CVD prevention measures. The pre-training assessment will serve as the source for estimation of baseline levels of knowledge for the trainer(s) to understand how much the CHWs already know about CVD risk factors, identify knowledge gaps, and customize training material to address these areas during training. The same tool will be administered after the training sessions to evaluate changes in knowledge of the CHWs. A follow-up assessment will be done at the end of the study (12 months) to all CHWs in the intervention arm to assess knowledge decay over time.

#### Baseline survey

A cross-sectional survey will be conducted in all selected villages at the beginning of the study and before randomization. Trained research assistants will conduct face-to-face interviews in Swahili with selected members of the community using a questionnaire. The questionnaire will be developed in English, translated into Swahili, and back-translated to English to check if it retained its original meaning. Collected data will include sociodemographic characteristics, knowledge on CVD risk factors, modifiable CVD risk behaviors (smoking, alcohol consumption, and dietary habits), and physiological CVD risk factors (elevated blood pressure, overweight, obesity, and elevated fasting blood glucose). Participants found to have elevated blood pressure and elevated fasting blood glucose during the baseline survey will be given referral notes to a health facility for further evaluation and appropriate management using standard Tanzanian guidelines.

#### Follow-up

Participants in the intervention study will be followed up by CHWs at home every month for the first six months, then bi-monthly up to 12 months. In addition to the health education provided during home follow-up visits, CHWs will also monitor and measure blood pressure, adherence to medication (if on medication), and provide further counseling on risk factors and continued healthy lifestyle promotion.

#### End-line survey

An end-line evaluation survey for participants in the intervention study will be conducted by an independent team. Outcome variables of interest assessed during baseline will be re-assessed during end-line to allow for assessment of changes in blood pressure, knowledge, and proportion of CVD risk factors following the CHWs delivered interventions.

#### Focus group discussions

We will conduct FGDs at the end of the intervention to assess the perception of participants about quality and acceptability of CHWs to deliver CVD-specific interventions for prevention of CVD risk factors. FGDs will be conducted for intervention participants and key community members (local political and religious leaders). Each FGD group will consist of 8–10 participants. FGDs will be conducted separately for intervention participants and key community members. An FGD guide with questions related to perceptions about quality and acceptability of the CHWs to deliver CVD-specific interventions will be used to lead the discussions. All FGDs will be audio recorded using an Olympus digital voice recorder.

#### Measurements of social and cardiovascular risk factors

##### Knowledge about CVDs

Knowledge about CVDs will be assessed using a structured questionnaire with variables adopted from other sources [36, 37]. Assessment of knowledge about CVDs will comprise the following knowledge domains: (1) causes and risk factors for CVD; (2) warning signs for CVD events; (3) course of action to be taken in case of CVD events; (4) unhealthy dietary habits; and (5) CVD prevention measures.

##### Blood pressure

Blood pressure will be measured using a standardized digital blood pressure machine (OMRON HEM-712C). Blood pressure will be measured on the left arm with the participant in a seated position. The first reading will be taken after resting for at least 5 min. The second and third readings will be taken halfway and at the end of interview, respectively. An average of three readings will be used in the analysis. Participants with elevated blood pressure will have measurements repeated on the following days to confirm their elevated blood pressure. Hypertension will be defined as average SBP ≥ 140 mmHg and/or DBP ≥ 90 mmHg and/or current treatment with antihypertensive medications in accordance with the Seventh Report of the Joint National Committee on Prevention, Detection, Evaluation and Treatment of High Blood Pressure [38].

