
Following the training, CHWs in the intervention villages will provide health education to raise awareness about CVD risk factors and promote healthy lifestyles during home visits. The health messages will focus on information pertaining to the deleterious effects of CVD risk factors, maintaining normal/ideal body weight, smoking cessation, reduction of excessive alcohol drinking, reduction of salt intake, increased consumption of fruits and green leafy vegetables, use of vegetable cooking oil, and use of unrefined cereals. CHWs will also review and provide flyers/brochures on CVD risk factors to participants for their reference. CHWs will use motivational and effective communication for behavior change to encourage participants to change unhealthy lifestyle behaviors.3.Referral and linkage to health facility

In both the intervention and control villages, participants found to have elevated blood pressure and elevated fasting blood glucose during the baseline survey will be given referral notes to the health facility for further evaluation and appropriate management using standard Tanzanian guidelines. For intervention villages, CHWs will conduct routine follow-ups and ask about their attendance to health the facility as they were advised. For those who will have not attended, reasons for non-attendance will be inquired. The intervention package is summarized in Table 1 below.

**Table 1 Tab1:** Summary of activities and assessments for intervention and control villages

Activity	Interventions and assessments	
	Intervention villages	Control villages
1. Baseline cross-sectional survey a. Sociodemographic characteristics b. Knowledge of CVD risk factors c. Proportion of CVD risk factors	Yes	Yes
2. Pre-training assessment of CHWs on knowledge about CVD risk factors	Yes	–
3. Training of CHWs on interventions for CVD prevention	Yes	–
4. Post-training assessment of CHWs on knowledge about CVD risk factors	Yes	–
5. Monthly CHW home-delivered interventions (M1–M6) a. Home health education b. Healthy lifestyle promotion c. Measurements (BP and anthropometrics)	Yes	–
6. Bi-monthly CHW home-delivered interventions (M7–M12) a. Home health education b. Healthy lifestyle promotion c. Measurements (BP and anthropometrics)	Yes	–
7. Focus group discussions for perceived quality and acceptability of CHWs to deliver CVD-specific interventions	Yes	–
8. Post-intervention assessment of CHWs for knowledge decay	Yes	–

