### Outcome measures

#### Primary outcome

The primary outcome measure is change in mean systolic blood pressure at 12 months in the intervention villages compared to control villages. The study aims to detect a mean change of ≥ 6.5 mmHg in systolic blood pressure (SBP) in the intervention villages compared to control villages.

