This study has some limitations worth mentioning. First, there is no guarantee of comparable distribution of sociodemographic characteristics such as age and sex between intervention and control villages. Therefore, the true effect of the CHW interventions may be distorted by the natural progression of the diversity in the pattern of CVD risk factors. These variations will be minimized by using multi-level analysis with random effect models. Second, the diagnosis of hypertension using blood pressure readings taken on a single visit may overestimate the true prevalence of hypertension in the population. However, using an average of three blood pressure measurements (halfway and at the end of interview) will minimize the risk of white coat hypertension. Additionally, we will repeat the measurements on a separate occasion for individuals with elevated blood pressure to confirm hypertension. The risk of contamination of the intervention will be minimized by grouping and randomizing a group of three close villages to the same intervention arm. This will ensure that for each district, intervention villages will be together but far away (approximately 20 km) from control villages. There are still chances of interaction between people in the intervention and control villages. Other limitations of the study include unmeasured residual confounding and measurement bias for anthropometric measurements.

In conclusion, this study is the first randomized trial investigating the feasibility and effectiveness of CHW home-delivered interventions for the reduction of CVD risk factors in Tanzania. The findings of this study may be beneficial in influencing policy changes to enhance home delivery of health education, screening, and healthy lifestyle promotion interventions for the reduction of CVD risk factors in communities using CHWs.

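### The analysed SBP includes the first reading, while only the intervention arm has scheduled BP measurement between surveys; extra habituation there would enter the primary effect

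*Protocol article*

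**What the plan says.** The primary outcome section of the protocol article reads: "The primary outcome measure is change in mean systolic blood pressure at 12 months in the intervention villages compared to control villages". The Blood pressure section fixes how SBP is obtained: "The first reading will be taken after resting for at least 5 min", then "The second and third readings will be taken halfway and at the end of interview, respectively", and "An average of three readings will be used in the analysis". The analysed value is therefore the plain mean of three readings, one of them before the interview.

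The Follow-up section says intervention-study participants are "followed up by CHWs at home every month for the first six months, then bi-monthly up to 12 months", and that "CHWs will also monitor and measure blood pressure, adherence to medication (if on medication" are part of these visits. Table 1 lists "Measurements (BP and anthropometrics" among the CHW visit activities in both the monthly and the bi-monthly rows, marked for intervention villages and blank for control villages. The Abstract states that, apart from referral at baseline, control villages get no CHW-delivered intervention.

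The Data analysis section estimates the effect as the month-12 minus baseline change in mean SBP, intervention minus control. The Discussion mentions the white-coat response only as a threat to the prevalence estimate, and says that "using an average of three blood pressure measurements (halfway and at the end of interview) will minimize the risk of white coat hypertension".

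**The concern.** The first reading of a visit is the one most exposed to an alerting response, and familiarity with the cuff may reduce that response. The documents state neither point; both are assumptions here. Under this design, intervention participants would reach the end-line survey after about nine home measurements, and controls after none scheduled by the study. Habituation common to both arms cancels in the difference-in-differences. Habituation that builds up after baseline in one arm does not.

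The error would lower end-line SBP in the intervention arm and so favour the intervention. It would look like the lifestyle effect the trial is seeking. The independent end-line team protects against assessor bias but does not address habituation in participants.

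**Working it through.** **Inputs from the protocol article.** Target difference 6.5 mmHg, SD 15 mmHg, intra-cluster correlation 0.03, attrition 20%, 258 participants in six villages per arm, 80% power, two-sided 5% (Sample size estimation; Data analysis). CHW visits: 6 monthly + 3 two-monthly = 9 (Follow-up; Table 1).

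**Inputs assumed.** First-reading excess over the later readings: 3-6 mmHg. Share of it lost in the intervention arm only: 25-100%. Within-visit SD of a single reading: 5-7 mmHg.

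**1. The plan's own sample size, to obtain a standard error.** Without clustering, 2 × (15 × (1.96 + 0.84) / 6.5)² gives 84 per arm. With 43 per village the design effect is 1 + 42 × 0.03 = 2.26, and 84 × 2.26 / 0.8 gives 238, which is not the stated 258. A cluster-level t calculation with 10 degrees of freedom does match:
- completers per arm: 258 × 0.8 = 206.4, or 34.4 per village
- design effect: 1 + 33.4 × 0.03 = 2.002
- SE: 15 × √(2 × 2.002 / 206.4) = 2.09 mmHg
- power at 6.5 mmHg: 80.0%

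The sample size is not in dispute. The SE serves only as a yardstick for the bias.

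**2. How a first-reading loss reaches the estimate.** The analysed value is (r1 + r2 + r3) / 3. If r1 falls at end-line by (excess × share) in the intervention arm only, the difference-in-differences shifts by (excess × share) / 3.

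**3. Size over the assumed range.** The last column is the chance of a significant result with no true effect (t, 10 df, SE 2.09), against a nominal 5%.

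| Excess (mmHg) | Share lost | Bias (mmHg) | % of 6.5 | Chance of significance |
|---|---|---|---|---|
| 3 | 25% | 0.25 | 4% | 5.1% |
| 3 | 50% | 0.5 | 8% | 5.5% |
| 3 | 100% | 1.0 | 15% | 7.2% |
| 6 | 25% | 0.5 | 8% | 5.5% |
| 6 | 50% | 1.0 | 15% | 7.2% |
| 6 | 100% | 2.0 | 31% | 14.0% |

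**4. What would be needed to produce the whole target.** 6.5 × 3 = 19.5 mmHg of first-reading loss in one arm only, far outside the assumed range.

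**5. Precision cost of dropping the first reading.**
- SD 5: 25/2 − 25/3 = 12.5 − 8.3 = 4.2; 4.2 / 225 = 1.9%
- SD 7: 49/2 − 49/3 = 24.5 − 16.3 = 8.2; 8.2 / 225 = 3.6%

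**6. What dropping it leaves behind.** If the loss is confined to r1, the mean of r2 and r3 carries none of it. If r1 loses 6 mmHg and r2 and r3 lose 4 mmHg each, the three-reading bias is (6 + 4 + 4) / 3 = 4.7 mmHg and the two-reading bias is still 4.0 mmHg.

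**The case against.** A three-reading mean, specified in advance and taken the same way in both arms and at both surveys, is not in itself an error. The mechanism and every mmHg figure for it come from outside the documents. The protocol also has features that work against the bias:

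- The first reading follows at least five minutes of rest.
- Participants with elevated BP, who are the trial population, have readings repeated on following days. Villages are allocated only after the baseline survey, so both arms share that exposure.
- Unfamiliar end-line assessors may still provoke an alerting response in people used to a village CHW.

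All of this stands. It argues for a smaller bias, but none of it makes habituation equal in the two arms.

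Four stronger readings are tempting and are not supported:

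- **Controls have no BP measurement at all between surveys.** Table 1 lists study activities only. Participants with elevated BP in both arms are referred to a health facility, where BP may be taken. Attendance is unknown.
- **The Discussion defines a different analysis variable.** It too says three measurements are averaged. Its parenthesis names only two of the time points, which is loose wording in a paragraph about prevalence.
- **The bias could account for the target effect.** That would need a one-arm first-reading loss of 19.5 mmHg.
- **Dropping the first reading cures the problem.** Habituation in the later readings would remain.

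**Conclusion.** The point holds as a cheap improvement to the definition of the primary measurement. The documents establish that the first reading has one-third weight, that scheduled CHW measurement between surveys occurs in one arm only, and that the difference-in-differences cannot remove habituation arising in that arm after baseline. The direction of any such bias favours the intervention.

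The size is not established. On the assumed inputs it is about 0.25-2.0 mmHg, or 4-31% of the target. The upper end requires the whole of a 6 mmHg excess to vanish in intervention participants and none of it in controls. The rest period, the repeat readings before allocation and facility visits by controls make the lower part more plausible, where the false-positive risk stays close to 5%.

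**What to change.** In the Blood pressure section, define analysis SBP and DBP, in both arms and at both surveys, as the mean of the second and third readings. Report the three-reading mean as a sensitivity analysis. As an editorial point, complete the parenthesis in the Discussion so that it agrees with the Blood pressure section and with the revised definition.

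The cost is a sentence or two. All three readings are already planned, and the Trial status section says recruitment has not started, so the definition can be settled before any data exist. The price is about 2-4% more variance under the assumed within-visit SD. The remedy is partial, and the limitations paragraph should say that habituation affecting the later readings in the intervention arm cannot be excluded.

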##### Blood glucose

Fasting blood glucose will be measured the next day using a Gluco plus glucometer point-of-care device following overnight fasting (at least 8 h of fasting). Elevated fasting blood glucose will be defined as ≥ 126 mg/dL or ≥ 7.0 mmol/L [39].

##### Behavioral risk factors

A modified WHO STEPwise data collection tool for surveillance of non-communicable diseases will be used to gather information on behavioral CVD risk factors including smoking, alcohol drinking, and dietary habits. The WHO STEPwise data collection tool has already been used in Tanzania for the assessment of behavioral CVD risk factors [35]. Questions will probe on current and past smoking as well as current and past alcohol drinking. Dietary assessment will include intakes of fruits, vegetables, salt, use of vegetable cooking oil, and consumption of whole grains.

##### Anthropometrics

Anthropometric measurements will include weight, height, and waist circumference taken using standard procedures. Briefly, all anthropometric measurements will be taken with the participant wearing light clothing and without shoes within the participant’s household compound. Body weight will be taken to the nearest 0.1 kg using a SECA digital scale placed on flat ground. Height will be taken in a standing position with heels perpendicular to the portable stadiometer, measured to the nearest 0.1 cm. BMI will be calculated as body weight divided by height squared (kg/m^2^). Overweight will be defined as BMI ≥ 25 kg/m^2^ but < 30 kg/m^2^ and obesity is defined as BMI ≥ 30 kg/m^2^ [40]. Waist circumference will be measured and recorded to the nearest 0.1 cm using a non-stretchable measuring tape at the mid-point between the lower margin of the last rib in the mid-axillary line and the iliac crest according the WHO guidelines [41]. Abdominal obesity will be defined as waist circumference ≥ 102 cm.

##### Socioeconomic status

Data on ownership of household items such as radio, television, telephone, sofa, refrigerator, bicycle, car, and having working electricity; house ownership, construction materials (floor, walls, and roofing materials); source of fuel for cooking and lighting; source of water supply for home use and drinking; and sanitation facility will be collected [42]. A household wealth index in quintiles will then be generated following descriptions in the Demographic Health Survey toolkit [43].

##### Other data

Sociodemographic information including age, gender, marital status, education level, and occupation will be collected. These variables have already been used in population surveys in Tanzania [35, 42]. Age will be collected as a continuous variable. Education will be measured as years spent in school and highest education level attained. Marital status will be grouped into never married, married or living together, divorced or separated, and widowed at the time of data collection. Occupation will be assessed as a categorical variable as none or housewife, employed (public/private), peasant, petty business, and others. Schedule for enrolment, interventions, and assessments for this study are summarized in Fig. 2 below.

**Fig. 2 Fig2:**
[figure not shown]
*Schedule* for enrolment, interventions, and assessments

### Data analysis

#### Quantitative data

The statistical analyses will be conducted using IBM SPSS statistics version 20, following the Consolidated Standards for Reporting Trials (CONSORT) guidelines for cluster randomized trials [44]. In the initial analysis, baseline characteristics of participants in the intervention study will be compared between intervention and control arms to ensures an approximate balance in the distribution of both measured and unmeasured confounders. Primary analyses will follow the intention-to-treat principle at 12 months, where all participants will be analyzed in their assigned intervention arm regardless of whether they actually received the intervention or not. Participants who refuse/withdraw their consent to continue with study will be excluded from the final analyses.

The primary outcome for the study is continuous mean SBP measured at baseline and at the end of participant follow-up. Change in mean SBP between baseline and end of intervention will be analyzed using individual-level data to assess the effectiveness of CHWs’ interventions for the reduction of blood pressure in the intervention arm compared to control arm. Between-group and within-group differences in mean SBP will be calculated and compared using difference-in-differences (DID) methods [45]. This approach will compare changes in mean SBP between baseline and 12 months for intervention and control villages.

Thus, IMPACT = [Y_i (*t* = 12)_ – Y_i (*t* = 0)_] - [Y_c (t = 12)_ – Y_c (t = 0)_].

Where Y_i(t = 12)_ is mean SBP in the intervention villages at the end-line survey (12 months), Y_i(t = 0)_ is mean SBP in the intervention villages at baseline survey, Y_c(t = 12)_ is mean SBP in the control villages at the end-line survey (12 months); and Y_c(t = 0)_ is mean SBP in the control villages at the baseline survey.

Multi-level analysis with mixed-effects models will be used to account for inter-observer and intra-observer variations in the groups at different times (at baseline and at end-line assessments). The intervention effect size will be reported as mean differences with 95% CIs.

Similar methods of DID will be used for the analysis of secondary outcomes including changes in mean DBP, changes in the proportion of other CVD risk factors, and changes in 10-year risk for CVD event. The 10-year risk for CVD event will be estimated using the Globorisk office charts [46] specific for Tanzania. The Globorisk office chart is a simple instrument which requires age, SBP, self-reported smoking status, and gender to predict one’s 10-year risk for CVD event. For participants in the intervention, changes in 10-year risk will be assessed by comparing the risk at baseline and end-line assessment.

Missing data and loss to follow-up are major issues of concern as they may compromise inferences of any trial. Efforts will be made during trial implementation to ensure complete follow-up and minimize missing data and loss to follow-up. During analysis, we will assess the magnitude and compare the baseline characteristics of participants lost to follow-up and those with end-line assessment data to see if there is any specific pattern of missing and loss to follow-up. Since there is no single universal method for handling missing data in trials [47], it is difficult to decide a priori the best way to handle missing data for this study. The decision to exclude missing data from final analysis or use multiple imputation analysis will be made after examining the magnitude and pattern of missing data. For all analyses, a two-sided *p* value of ≤ 0.05 will considered statistically significant.

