### Sample size estimation

This will be a two-arm cluster randomized controlled trial using villages as units of randomization. The minimum sample size for the baseline cross-sectional survey is estimated according to the methods proposed in the WHO STEPwise approach to chronic disease risk factors surveillance (STEPS) [34]. The sample size is calculated for 95% confidence intervals (CI) (z = 1.96) on the basis of a 5% margin of error and an estimated prior population prevalence of hypertension of 25.9% from the nation-wide representative STEPS survey in Tanzania [35], a design effect of 1 and an anticipated attrition rate of 20%. Participants will be adults aged 25–64 years and categorized into four age groups for each sex, resulting in eight strata. The resulting sample size is 2950. Participants with elevated blood pressure during the baseline survey will be eligible and invited to participate in the intervention study.

The sample size for the intervention study is calculated to provide an 80% power to detect a ≥ 6.5 mmHg difference in mean SBP between the intervention and control villages at an alpha level of 5%, assuming an attrition rate of 20%, an inter-cluster correlation of 0.03, and a standard deviation (SD) of SBP of 15 mmHg. The resulting sample size is 258 participants per arm of six villages. Thus, the total sample size for intervention study will be 516 participants from 12 villages.

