### Randomization and blinding

The unit of randomization will be the village. A total of 12 villages (six from each district) will be randomly selected from the list of villages with active CHWs. The selected villages from each district will be grouped into two groups of three villages based on population size, type of health facility serving the village, and geographical distance between villages. One group of three villages from each district will be randomly assigned to intervention and another to control. This will ensure that intervention villages are bundled together but far away from control villages, hence minimizing contamination. The final randomization of intervention and control villages will be done by a statistician who is not involved in the implementation of field activities. Randomization of villages to the intervention and control arms will be done by a senior statistician based at Muhimbili University of Health and Allied Science in Dar es Salaam, Tanzania. Assignment of villages to either the intervention or control arm will be done after the baseline survey. Given the nature of the intervention, it is not possible to blind the CHWs who will be involved in the delivery of the intervention. The study design and flow chart are shown in Fig. 1. The SPIRIT checklist is provided in Additional file 1.

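### The primary difference-in-differences fixes the baseline SBP slope at 1, and random effects are wrongly credited with correcting age and sex imbalance

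*Protocol article*

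**What the plan says.** Under Quantitative data, the primary effect is the change in mean SBP from baseline to 12 months in the intervention villages minus the same change in the control villages: "Between-group and within-group differences in mean SBP will be calculated and compared using difference-in-differences (DID) methods". The formula has no baseline slope and no covariate. Mixed-effects models are then added, with variation between and within observers at the two surveys as their stated purpose. No fixed covariates are named.

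The Discussion accepts that age and sex may differ between the arms and that the effect could be distorted as a result. It gives this remedy: "These variations will be minimized by using multi-level analysis with random effect models".

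Sample size estimation is "calculated to provide an 80% power to detect a ≥ 6.5 mmHg difference in mean SBP between the intervention and control villages", "assuming an attrition rate of 20%, an inter-cluster correlation of 0.03, and a standard deviation (SD) of SBP of 15 mmHg". No correlation between baseline and 12-month SBP is given.

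Under Randomization and blinding, "A total of 12 villages (six from each district) will be randomly selected from the list of villages with active CHWs". In each district the six villages form two groups of three, and one group is allocated to each arm. Assignment follows the baseline survey.

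**The concern.** Two statements need attention.

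First, subtracting baseline SBP treats every mmHg of baseline difference as if it would persist in full to 12 months. Participants enter the trial because of elevated blood pressure, so part of a high baseline reading is transient and the true individual-level slope is below 1. A change-score contrast therefore carries more noise than baseline adjustment generally would. If the arms differ at baseline by chance in that transient part, it subtracts too much.

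Second, random effects are offered as the remedy for unequal age and sex. A random village effect describes correlation within villages and mainly affects the standard error. It does not remove a covariate difference from the arm contrast; a fixed covariate term does. With only 12 villages, allocated in bundles, chance imbalance is a realistic prospect, and the article would rely on a tool that does not address it.

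**Working it through.** **Inputs from the article.** Two-sided alpha 0.05, power 80%, difference 6.5 mmHg, SD of SBP 15 mmHg, ICC 0.03, attrition 20%, six villages and 258 participants per arm (43 per village). **Assumed:** the correlation r, shown over 0.3 to 0.7.

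**1. The article's own figure.** With t on 10 df, the multiplier is 2.228 + 0.879 = 3.107.
- Unclustered n per arm: 2 × 15² × 3.107² / 6.5² = 102.83.
- Analysed per village: 102.83 × 0.97 / (6 − 0.03 × 102.83) = 34.22.
- With attrition: 34.22 / 0.8 = 42.8, rounded up to 43; 43 × 6 = 258.

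The figure reproduces exactly as a two-sample comparison of SBP with SD 15.

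**2. Planned contrast against baseline adjustment.** With equal SDs at both times, the variance multiplier is 2(1 − r) for the change score and 1 − r² for baseline adjustment (ANCOVA). The ratio is (1 + r)/2. With 43 × 0.8 = 34.4 analysed per village, the design effect is 1 + 33.4 × 0.03 = 2.002, and the SE at multiplier 1 is 15 × √(2 × 2.002 / 206.4) = 2.09 mmHg. Power uses the noncentral t on 10 df, with villages as independent units and the same correlation at village and individual level.

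| r | Variance ratio | SE, DID | SE, ANCOVA | Power, DID | Power, ANCOVA |
|---|---|---|---|---|---|
| 0.3 | 0.65 | 2.47 | 1.99 | 66% | 84% |
| 0.5 | 0.75 | 2.09 | 1.81 | 80% | 90% |
| 0.7 | 0.85 | 1.62 | 1.49 | 95% | 97% |

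The SD of change is 15 × √(2(1 − r)), which equals 15 only at r = 0.5. Enrolment per arm needed for 80% power by DID is 624, 258 and 114 at r = 0.3, 0.5 and 0.7.

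**3. Where the gain shrinks.**
- Sharp selection on SBP. Assume a population N(128, 20²) cut at 140: the baseline SD falls to about 10.05 (variance 101.1). The change variance is (1 − r)² × 101.1 + 400(1 − r²), against 400(1 − r²) after adjustment. At r = 0.6 this is 272.2 against 256, ratio 0.94; at r = 0.8, 148.0 against 144, ratio 0.97. Power is 72% against 75% at r = 0.6, and 93% against 94% at r = 0.8.
- Stable village means. Assume individual r = 0.3 and village-level correlation 0.9. Per village mean, the between-village variance is 225 × 0.03 = 6.75 and the within-village variance 225 × 0.97 / 34.4 = 6.34. DID: 0.2 × 6.75 + 1.4 × 6.34 = 10.23. ANCOVA with slope 0.3: 6.75 × (1 + 0.09 − 0.54) + 6.34 × 0.91 = 9.49. The ratio is 0.93, and power 89% against 91%.

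**4. Over-correction.** For a chance individual-level baseline difference d, the change score is off by −(1 − slope) × d. At SD 15, the SE of the individual-level part of the baseline difference is √(2 × 225 × 0.97 / 258) = 1.30 mmHg. A two-SE difference (2.6 mmHg) with slope 0.5 to 0.7 gives an error of 0.8 to 1.3 mmHg, against a target of 6.5.

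**5. Random effects and imbalance.** In a simulation with 12 villages of 34, true effect 0, an assumed 4-year age imbalance and 0.5 mmHg per year, a village random intercept on end-line SBP gave 2.04 mmHg. Adding age as a fixed effect gave 0.01. DID in the same scenario gave 0.02, because an age effect that is constant over time cancels in the change.

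**6. Cost of a district term.** For ANCOVA at r = 0.5, if villages are the units, df go from 10 to 9 and power from 90% to 89%. If the four bundles are the units, df go from 2 to 1 and power from 49% to 22%, even with no extra bundle variance.

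**The case against.** DID is a legitimate, pre-specified estimator that matches an outcome defined as change, and it is unbiased over repeated randomisation. It cancels any imbalance whose effect on SBP is constant over time, and it removes persistent village differences exactly. An individual-level ANCOVA slope would under-correct those village differences. At 43 per village, 43 × 0.03 / 2.26 = 57% of the variance of the baseline arm difference is between villages. All of this stands. It means DID is not biased, and that an error calculated from the whole baseline difference would be overstated.

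A condensed article may also leave its covariate list to an analysis plan. That stands too: the absence of age, sex and district from the formula is not itself a fault. It does not rescue the Discussion sentence, which names the wrong mechanism whatever such a plan contains.

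A reader might infer three stronger things:
- **The trial is underpowered.** The article gives no r, and 258 per arm is adequate for DID at r of 0.5 or above.
- **Power would rise from 66% to 84%.** That is the favourable end, at r = 0.3 with equal SDs and equal correlations. Selection on high SBP works against it, although entry through diastolic pressure or treatment makes truncation incomplete.
- **District should simply be added because allocation was within district.** Each arm has three villages per district by design, and the df cost may be large if bundles are the units.

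**Conclusion.** The point holds in limited form. The Discussion's claim about random effects is wrong irrespective of any assumption about r. DID protects against age or sex imbalance only where its effect is constant over time, whereas the Discussion's worry is about risk factors changing over time.

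The change-score analysis is valid but generally less precise than baseline adjustment, and it over-corrects chance individual-level differences. How much precision is lost cannot be fixed from the article. The variance ratio runs from 0.65 under favourable assumptions to about 0.97 under sharp truncation. The conditional error is about 1 mmHg for a two-SE individual-level difference, given an assumed slope of 0.5 to 0.7. The sample size rests on "a standard deviation (SD) of SBP of 15 mmHg", which matches the planned contrast only at r = 0.5; that is an unstated assumption, not a demonstrated shortfall.

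**What to change.** - Make the primary model a linear mixed model for 12-month SBP with fixed effects for arm, baseline SBP, age and sex, and a random effect for clustering. Baseline precedes allocation, so adjusting for it is sound.
- Keep DID as a sensitivity analysis.
- Reword the Discussion: fixed covariates handle measured imbalance; random effects handle clustering.
- State the r assumed in the sample size.
- Add a district term only with its df cost stated: 1 of 10 if villages are the units, 1 of 2 if the four randomised bundles are.

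The cost is wording. Baseline SBP, age and sex are already collected, and the article reports that recruitment has not begun. Baseline adjustment does not solve the separate problem of having only four randomised bundles.
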